### Procedure

Eligible patients will be randomized to either study groups (acupuncture plus conventional treatment) or control groups (conventional treatment alone) based on the size and side of their TH. After successful randomization, neurological assessments will occur at four time points: before treatment sessions begin, 30 days after onset of TH, at the end of treatment (6 weeks), and 90 days after onset of TH.

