### Outcome measures

#### Primary outcome measure

The primary outcome measure will be NIHSS score, a measure of neurological status, at the end of treatment, at 30 days after TH, and at 90 days after TH. NIHSS is used to describe neurological deficits in stroke patients, and it strongly predicts the likelihood of a patient’s recovery after stroke. The NIHSS is comprised of 11 test items including level of consciousness, gaze, visual field defects, facial palsy, upper extremity motor, lower extremity motor, limb ataxia, sensory ability, language, dysphagia, and neglect. Total score ranges from 0 to 42, with scores above 25 indicating very severe neurological impairment, scores of 5 to 24 indicating moderately severe to severe impairment, and scores below 5 indicating mild impairment.

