#### Secondary outcome measures

Secondary outcome measures are as follows:Poor outcome, defined as death or major disability, is defined as a score of 3 to 6 on the modified Rankin scale at 90 days after onset of TH. Scores on the modified Rankin scale range from 0 to 6, with a score of zero indicating no symptoms; a score of five indicating severe disability, confinement to bed, or incontinence; and a score of six indicating death.The rate of surgery at 30 days is defined as the incidence of neurological deterioration requiring surgical intervention.The Glasgow Outcome Scale (GOS) at 90 days after onset of TH is a measure of long-term outcome and includes five grades: 5, good recovery; 4, moderate disability; 3, severe disability; 2, persistent vegetative state; and 1, death.The Barthel activities of daily living (ADL) index and the Rivermead Mobility Index will be performed on each patient at the end of treatment, at 30 days after TH, and at 90 days after TH.Patients with left thalamic hemorrhages will also be evaluated with several language tests including the Boston Naming Test, the Boston Diagnostic Aphasia Exam, the Western Aphasia Battery, and the Mount Wilga High Level Language Screening Test at the end of treatment, at 30 days after TH, and at 90 days after TH.Patients with right thalamic hemorrhages will also be evaluated for visual neglect with the Behavioral In-attention Test (BIT) at the end of treatment, at 30 days after TH, and at 90 days after TH.

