## Discussion

In this randomized controlled trial, we will observe the effect of acupuncture therapy on patients with acute TH. The findings of this project are expected to provide evidence for the efficacy of acupuncture in improving the prognosis of patients with moderate TH. To minimize bias, stratified block randomization will be used according to sex and age, and the outcomes reviewer will be blinded. Subjects will be treated alone in a treatment room in order to avoid any communication with other subjects.

Generally speaking, no ideal placebo-controlled acupuncture trials have been performed previously [34]. Because recent acupuncture trials have examined so-called sham acupuncture techniques, including: needling of acupuncture points through non-penetrating needles, needling of non-acupuncture points, and needling of acupuncture points that are not indicated for that specific condition, these prior trials have not accurately reflected TCM theory and therefore have not properly assessed it [34]. Further complicating things is that sham acupuncture has been shown to have some efficacy [35]. In China, many patients and their families have had acupuncture at some time in their lives or are at least familiar with the acupuncture process. Therefore, it would be difficult to design a trial assessing the utility of sham acupuncture versus real acupuncture while keeping the patient blinded.

The decision was made to examine patients with left sided TH separately from patients with right sided TH. In the majority of patients, Broca’s cortical area and Wernicke’s cortical area are located in the left hemisphere. Therefore, patients with left hemisphere stroke (ischemic or hemorrhagic) are at risk for language deficits. Similarly, patients with right sided insults are at risk for symptoms of visual neglect. Both language deficits and visual neglect can have a profound impact on the way a patient responds to treatment and rehabilitation of other neurologic deficits. Therefore, to account for the potentially confounding effects of language deficits and visual neglect respectively, patients were subdivided into right and left TH subgroups.

Along the same lines, not all patients have their language centers located in their left hemisphere. While the majority of left handed patients have their language centers in the left hemisphere, some do have them in the right hemisphere. Therefore, in this study, we have only included right handed patients.

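### Splitting by side does not account for language deficit or neglect; use the pre-treatment NIHSS language and neglect items when analysing the side-specific tests

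*Protocol article*

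**What the plan says.** All references are to the protocol article.

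- **Purpose of the split (Discussion).** Language deficit and neglect are said to have a large influence on how patients respond to treatment and rehabilitation. Hence, "to account for the potentially confounding effects of language deficits and visual neglect respectively, patients were subdivided into right and left TH subgroups".
- **What side tells us (Discussion).** On the left, "patients with left hemisphere stroke (ischemic or hemorrhagic) are at risk for language deficits"; on the right, "patients with right sided insults are at risk for symptoms of visual neglect". No proportion is given for either. The eligibility criteria require neither deficit; the only related criterion is right-handedness.
- **Who is tested, and when (Secondary outcome measures).** "Patients with left thalamic hemorrhages will also be evaluated with several language tests", the last of them being "the Mount Wilga High Level Language Screening Test at the end of treatment, at 30 days after TH, and at 90 days after TH". For the other side, "Patients with right thalamic hemorrhages will also be evaluated for visual neglect with the Behavioral In-attention Test (BIT) at the end of treatment", and again at 30 and 90 days. No deficit is required for testing, and no pre-treatment time is listed.
- **What is available before treatment.** Under Procedure, neurological assessments include one "before treatment sessions begin, 30 days after onset of TH" being the next. The instrument is not named there, but the abstract defines the primary outcome as a change in NIHSS, which implies a baseline NIHSS. Its items include "limb ataxia, sensory ability, language, dysphagia, and neglect" (Primary outcome measure).
- **Allocation and analysis.** Randomization and blinding gives 1:1 allocation by size and side. Statistical analysis names Student's t, Mann-Whitney, Fisher's exact and Pearson's tests, with no baseline covariate.

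**The concern.** If the deficits matter as much as the Discussion says, what matters is who has one, and side does not show that. Within the left-sided patients, some will have a language deficit at entry and some will not; the same holds for neglect on the right.

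For the language tests and the BIT this has two consequences. If acupuncture acts only on an existing deficit, patients without one contribute no effect, so the mean difference shrinks in proportion to the share affected. The spread between affected and unaffected patients also adds to the error variance of an unadjusted comparison. With no pre-treatment score listed for these tests, they supply neither a change score nor a baseline covariate of their own.

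At stake is the information that these secondary endpoints can give. They matter because the Discussion adds further tests on the ground that the NIHSS alone is not comprehensive enough.

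**Working it through.** **1. The plan's own figure.** Sample size calculation gives SD 4.2, difference 2.3, α = 0.05 and 80% power. Statistical analysis makes the test two-sided.

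n per arm = 2(1.960 + 0.842)² × 4.2² / 2.3² = 52.3, so 53. Allowing 10% non-adherence plus 3% loss: 53 / 0.87 = 60.9, so 61. Then 61 × 8 = 488, as stated. The total therefore sizes one comparison of 61 against 61 in each side-by-size stratum, on NIHSS. No calculation is given for language or neglect.

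**2. Model for a side-specific test.** None of these inputs is in the protocol; all are assumptions.
- p = share of patients on that side with the deficit at baseline.
- D = gap in mean score between affected and unaffected patients, in SDs of the affected.
- Unaffected SD = 0.1; effect = 0.5 SD in affected patients only.
- n = 122 per arm, that is, both size strata of one side pooled (61 + 61).

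Mean difference = 0.5p. 
Variance, unadjusted = p + (1 − p) × 0.01 + p(1 − p)D². 
Variance, perfectly adjusted for deficit = p + (1 − p) × 0.01. 
Power is from a two-sided t-test at 5%.

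Example, p = 0.3 and D = 2: variance = 0.300 + 0.007 + 0.840 = 1.147, SD 1.071. The difference is 0.15. Noncentrality = (0.15 / 1.071) × √(122/2) = 1.09, so power is about 19%. Adjusted: variance 0.307, SD 0.554, noncentrality 2.11, power about 56%.

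| p | D | Unadjusted | Perfectly adjusted |
|---|---|---|---|
| 0.3 | 2 | 19% | 56% |
| 0.3 | 3 | 12% | 56% |
| 0.5 | 2 | 35% | 78% |
| 0.5 | 3 | 22% | 78% |
| 0.5 | 1 | 61% | 78% |
| 0.8 | 2 | 74% | 94% |
| 0.8 | 1 | 89% | 94% |

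With unaffected SD 0.5, p = 0.5 and D = 1, the figures are 55% and 69%.

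**3. An imperfect baseline item.** Assume the NIHSS item detects the deficit with 70% sensitivity and 90% specificity. The adjusted variance then keeps a term D² × [P₁q₁(1 − q₁) + P₀q₀(1 − q₀)], where P₁ and P₀ are the shares rated positive and negative, and q₁ and q₀ the shares truly affected among them.

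- p = 0.3: P₁ = 0.28, q₁ = 0.75, q₀ = 0.125, bracket = 0.131. Variance is 0.832 (D = 2) or 1.488 (D = 3); power 25% or 16%.
- p = 0.5: P₁ = 0.40, q₁ = 0.875, q₀ = 0.25, bracket = 0.156. Variance is 1.130 or 1.911; power 45% or 29%.

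Adjusted power is thus 16–45%, against 12–35% unadjusted.

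**4. Stratum-level analysis.** At 61 per arm, perfect adjustment gives about 32% (p = 0.3) and 49% (p = 0.5).

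**5. What adjustment does not do.** It removes the variance term; the side-wide mean difference stays at 0.5p. Only an analysis in patients with a baseline deficit addresses the undiluted effect.

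**The case against.** **Confounding.** A reader might infer that the trial's control of confounding fails. The protocol does not support that. Allocation is 1:1 within side and size, so deficits are balanced between arms in expectation. What remains is chance imbalance, dilution and lost precision on secondary endpoints. This stands.

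**No baseline information.** A reader might infer that language and neglect are not assessed at all before treatment. That is too broad. A pre-treatment neurological assessment is planned, and the NIHSS has items for both. The NIHSS times under Primary outcome measure also omit baseline although a change score is defined in the abstract, so the lists may give outcome times only. This stands, and the point is confined to the dedicated tests.

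**Swamped endpoints.** A reader might infer that the side-specific endpoints will be uninformative. Prevalence, gap, spread and effect are all assumed, and the loss is small at high prevalence with a small gap. A ceiling in unaffected patients is also an assumption; one of the tests is a high-level language screen. This stands.

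**Purpose of the split.** The Discussion ties the split to recovery from other deficits and does not say that the side-specific tests justify it. True, but the sentence still credits side with something that it cannot do.

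**Left to the SAP.** Covariates and subgroups for secondary endpoints are commonly settled there, and the article does not state which patients enter each comparison. Silence on covariates is therefore not an omission to be held against the article. But the article does state a rationale that is wrong as worded and names unadjusted tests, and a better use of data already planned is available.

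**Conclusion.** The point holds in a limited form. Side determines which deficit a patient is at risk of; it does not account for who has it, so the Discussion overstates what the split achieves. With the dedicated tests listed only after treatment starts and unadjusted tests stated, baseline deficit may dilute the language and BIT endpoints and reduce their precision.

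The protocol does not determine the size. Using the pre-treatment item raised power in every case tried, from a few percentage points (high prevalence, small gap, or an inaccurate item) to more than 40 (low prevalence, wide gap, accurate item). These figures assume 122 per arm. They take no account of deaths, although the Background cites mortality above 30% in moderate TH, or of untestable patients.

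This concerns secondary endpoints only. The primary NIHSS comparison is not invalidated, and the 488 reproduces.

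**What to change.** 1. Analyse each language test in left-sided patients with the pre-treatment NIHSS language item (0 against 1 or more) as a covariate or stratum. Analyse the BIT in right-sided patients in the same way with the pre-treatment NIHSS neglect item.
2. Report the effect in patients with a baseline deficit as a supportive analysis, specified in advance.
3. State that the pre-treatment assessment includes the NIHSS with its item scores recorded.
4. Reword the Discussion sentence: side determines which tests are given, and baseline deficit is handled through these items.

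The cost is wording in the analysis section and the Discussion, with no new visits, tests or patients. The downside is small: the NIHSS items are coarse, so the gain may be well below the perfect-adjustment figures, and some patients may be untestable at baseline, so a rule for coding them is needed.

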### Subject enrollment

The nurses responsible for the neurosurgery patients at Huaxi Hospital will be thoroughly educated regarding moderate TH. Patients and/or their legal guardians will be able to contact the project leader at any time should they desire additional information. After obtaining signed informed consent, the project leader will collect certain baseline information (including age, diagnosis, side of hemorrhage (left or right), hematoma volume, medical history, CT report, etc..) and determine whether or not the patient meets the eligibility criteria for the trial or not. Only participants who meet the inclusion criteria and do not possess any of the exclusion criteria will be enrolled. A total of 488 patients with TH who are admitted to the neurosurgical unit of our hospital will be enrolled in the trial.

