### Statistical analysis

The results will be presented as mean score plus or minus standard deviation and as percentages. Categorical data will be analyzed with Fisher’s exact test or the Mann-Whitney U test where appropriate. Continuous data will be analyzed with the Student’s t test or Pearson’s test where appropriate. Multi-ranked data will be analyzed using the Mann-Whitney U test. Differences will be considered statistically significant at *P* < 0.05 (two-tailed). All statistical analyses will be performed using the Statistical Package for the Social Sciences (version 13.0; SPSS; Chicago, Illinois, USA).

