Another potentially confounding factor is the involvement of adjacent brain tissue as a secondary result of the initial thalamic insult. Adjacent brain tissue can necrose either directly via extension of the thalamic bleed or indirectly via mass effect from the thalamic bleed and/or edema related to the thalamic bleed. Areas at specifically high risk include the genu of the internal capsule which lies lateral to the thalamus, the posterior limb of the internal capsule which lies posterolateral to the thalamus, the anterior limb of the internal capsule which lies anterolateral to the thalamus, and the peri-thalamic/peri-ventricular white matter which lies superior to the thalamus. Involvement of the genu of the internal capsule, the posterior limb of the internal capsule, and adjacent white matter could result in paralysis. Involvement of the posterior limb of the internal capsule could also result in sensory loss or impaired comprehension [36]. Finally, involvement of the anterior limb of the internal capsule could result in cognitive issues. Involvement of any of these areas could potentially impact how a patient recovers and/or sway the post-stroke assessment scores in one direction or another depending on how many of the affected patients ended up in the control group or the intervention group. To combat this, we utilized two mechanisms. First, we excluded patients from the study whose TH on admission CT demonstrated extension of the insult beyond the thalamus. However, admission CT often does not disclose the true area affected by the insult. CT performed 90 days later is much more sensitive in demonstrating the insult’s true encompassment. We therefore further subdivided the groups by size. While all subjects in the study have moderate thalamic hemorrhage, groups were further subdivided into subjects with 10–15 cc of TH and 15–30 cc of TH. Patients with 10–15 cc of TH are much less likely to experience insults to brain tissue external to the thalamus than patients with 15–30 cc of TH as a result of the smaller size of the initial bleed. We also plan to retrospectively analyze the results of CT scans performed 90 days following the insult to determine what percent of patients in each group experienced extension of their primary insult to tissue beyond the thalamus and how this may have affected the results in that group. After dividing patients by side of hemorrhage and size of hemorrhage four intervention groups were established, and along with the corresponding four control groups, this totaled eight distinct subject groups.

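### A single 15 cc cut and an unadjusted t test leave recorded hematoma volume unused, which costs some precision, mainly in the 15–30 cc comparisons

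*Protocol article*

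**What the plan says.** The Discussion of the protocol article treats involvement of tissue next to the thalamus as a possible confounder. Such involvement could "sway the post-stroke assessment scores in one direction or another depending on how many of the affected patients ended up in the control group", and how many in the acupuncture arm. The article then writes "To combat this, we utilized two mechanisms". The first is exclusion of patients whose admission CT shows extension beyond the thalamus, which is also listed under Exclusion criteria. The article concedes that admission CT often misses the true extent, and for that reason adds the second mechanism, the size split: "groups were further subdivided into subjects with 10–15 cc of TH and 15–30 cc of TH". Its rationale is that "Patients with 10–15 cc of TH are much less likely to experience insults to brain tissue external to the thalamus" than those with 15–30 cc. It gives no extension rates for either band. It adds a later step: "We also plan to retrospectively analyze the results of CT scans performed 90 days following the insult".

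Under Subject enrollment, the baseline information includes "side of hemorrhage (left or right), hematoma volume, medical history, CT report", so the volume of each bleed is on file. Under Statistical analysis, "Continuous data will be analyzed with the Student’s t test" (or Pearson's test), with Fisher's exact and Mann-Whitney tests for other data types. No analysis that uses individual volume is named.

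**The concern.** The article treats the size of the bleed as the driver of injury outside the thalamus and then uses it only as a two-level grouping. The bands differ in width: 5 cc for 10–15 cc and 15 cc for 15–30 cc. Within a band, a plain t test compares the arms without regard to volume, so a 16 cc and a 29 cc bleed count as alike. The wider band is also the one that the article regards as more prone to outside injury. The coarse step is therefore weakest where its own reasoning says it matters most.

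At stake is the precision of the NIHSS comparison in the two 15–30 cc pairs (left and right). The sample size leaves those comparisons little slack. The Discussion also implies somewhat more protection than one cut can give.

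**Working it through.** **Inputs from the article.** SD of NIHSS 4.2; difference 2.3 points; 80% power; α = 0.05 two-sided; 10% non-adherence and 3% loss to follow-up; eight groups of 61, total 488; bands 10–15 cc and 15–30 cc.

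**Assumptions, not in the article.** Volume is uniform within each band; the two bands hold equal numbers; NIHSS rises linearly by 0.2 to 0.5 points per cc within a band.

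**1. The plan's own figure.** n per arm = 2 × (1.96 + 0.8416)² × 4.2² / 2.3² = 52.3, rounded up to 53. Then 53 / (1 − 0.13) = 60.9, rounded up to 61, and 61 × 8 = 488. The stated total is reproduced, and it shows that each size-by-side pair is sized for its own comparison with about 53 evaluable per arm.

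**2. How much volume variance the cut removes.** The variance of a uniform variable is width²/12.
- 10–15 cc: 25/12 = 2.08, SD 1.44 cc.
- 15–30 cc: 225/12 = 18.75, SD 4.33 cc.
- Mean within-band variance: (2.08 + 18.75)/2 = 10.42.
- Between-band variance, with band means 12.5 and 22.5: 0.25 × 10² = 25.
- Share remaining: 10.42/35.42 = 29%, so the cut removes about 71%.
- Share of the remainder in 15–30 cc: 18.75/(2.08 + 18.75) = 90%.

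If 25% to 75% of patients are in the smaller band, 44% to 25% of the variance remains. With right-skewed volumes and equal numbers, about 36% remains.

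**3. Chance difference in mean volume between arms.** The 95% range is ±1.96 × SD × √(2/53): ±0.55 cc in 10–15 cc and ±1.65 cc in 15–30 cc. For slopes of 0.2 to 0.5, this contributes ±0.33 to ±0.82 NIHSS points to the 15–30 cc contrast. It is a component of the contrast's ordinary sampling error, which is ±1.96 × 4.2 × √(2/53) = ±1.60 points in all.

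**4. Power after adjustment.** R² = (slope × SD of volume / 4.2)², and the residual SD is 4.2 × √(1 − R²). Power is from the noncentral t with 53 per arm and a difference of 2.3, ignoring the one degree of freedom spent. Unadjusted power is 79.8%.

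| Assumed slope (points/cc) | R², 15–30 cc | Power, 15–30 cc | Power, 10–15 cc |
|---|---|---|---|
| 0.2 | 0.043 | 81.4% | 79.9% |
| 0.3 | 0.096 | 83.6% | 80.2% |
| 0.4 | 0.170 | 86.6% | 80.5% |
| 0.5 | 0.266 | 90.3% | 80.9% |

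**5. Link from volume to extension.** If the risk of extension rose linearly across 15–30 cc from 20% to 60%, volume would explain about 6% of the variance in extension; from 10% to 90%, about 21%. Both gradients are assumed. Adjusting for volume therefore removes only a minor part of any imbalance in extension itself.

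**The case against.** The strongest reply is that an unadjusted comparison of randomised arms is valid. With 1:1 allocation, within-band volume variation is already in the outcome SD of 4.2 and so in the t test's standard error. That stands. The shift of ±0.33 to ±0.82 points is part of that error and must not be added to it, and the issue is efficiency only.

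A reader might infer that most of the imbalance survives the cut. The documents do not support that. For volume, 25–44% remains under the distributions tried. The 90% figure says where the remainder sits, not how large it is. For extension itself, assumed rates in the two bands from 5% and 30% to 5% and 80% leave 89% down to 42% of the variance. Where much remains, that is mainly because extension is a yes/no event only loosely tied to volume, not because of the width of the upper band.

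A reader might also infer that the split stands alone, or that day-90 CT is the only other step. Neither is so: exclusion on admission CT is the first mechanism, and the Discussion does not say that the split eliminates imbalance.

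The slopes are assumed, and the top one is demanding: 0.5 points per cc means 7.5 NIHSS points across 15–30 cc. If change in NIHSS is analysed, as the Abstract words it, the part of the volume effect already present at baseline drops out and the slope may be smaller. This also stands, and it is why the gain is given as a range with a low end of under 2 percentage points.

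Finally, covariates are often left to an analysis plan, which is not shown here. That the article does not name volume is therefore not proof that it will never be used. The point rests instead on what the article does state: a specific safeguard, its rationale, and a named test that makes no use of a value already collected.

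**Conclusion.** The point holds as a modest matter of precision. The size split is a sensible step and, under the uniform, equal-size assumption, takes out about 71% of volume variance. What is left lies about 90% in the 15–30 cc groups, and the named t test does not use it. Adjusting for volume would lift power in a 15–30 cc pair by somewhere between 2 and 11 percentage points (79.8% to between 81.4% and 90.3%) for slopes of 0.2 to 0.5 points per cc, and by about 1 point at most in 10–15 cc. The article gives no slope, so the true gain could lie at or below the low end.

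Nothing here shows bias or an invalid test. The planned 90-day CT analysis can describe extension in each group, but it is measured after randomisation and cannot stand in for a baseline variable.

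**What to change.** Keep the two size bands for allocation. Under Statistical analysis, replace the plain t test for NIHSS with a pre-specified linear model (ANCOVA) that includes treatment and admission hematoma volume in cc as a continuous, linear covariate.

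In the Discussion, say that the size split and the volume adjustment reduce, but do not remove, the effect of imbalance in extension risk, and that the 90-day CT analysis is descriptive because it is measured after randomisation. The text should not claim that volume adjustment deals with extension itself.

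The cost is one degree of freedom, an assumed linear form, and a few sentences of text. No new data and no extra patients are needed.
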